## Abstract

**Background:**

Depression is a disorder with high prevalence in primary health care and a significant burden of illness. The delivery of health care for depression, as well as other chronic illnesses, has been criticized for several reasons and new strategies to address the needs of these illnesses have been advocated. Case management is a patient-centered approach which has shown efficacy in the treatment of depression in highly organized Health Maintenance Organization (HMO) settings and which might also be effective in other, less structured settings.

**Methods/Design:**

PRoMPT (PRimary care Monitoring for depressive Patients Trial) is a cluster randomised controlled trial with General Practice (GP) as the unit of randomisation. The aim of the study is to evaluate a GP applied case-management for patients with major depressive disorder. 70 GPs were randomised either to intervention group or to control group with the control group delivering usual care. Each GP will include 10 patients suffering from major depressive disorder according to the DSM-IV criteria. The intervention group will receive treatment based on standardized guidelines and monthly telephone monitoring from a trained practice nurse. The nurse investigates the patient's status concerning the MDD criteria, his adherence to GPs prescriptions, possible side effects of medication, and treatment goal attainment. The control group receives usual care – including recommended guidelines. Main outcome measure is the cumulative score of the section depressive disorders (PHQ-9) from the German version of the Prime MD Patient Health Questionnaire (PHQ-D). Secondary outcome measures are the Beck-Depression-Inventory, self-reported adherence (adapted from Moriskey) and the SF-36. In addition, data are collected about patients' satisfaction (EUROPEP-tool), medication, health care utilization, comorbidity, suicide attempts and days out of work.

The study comprises three assessment times: baseline (T0) , follow-up after 6 months (T1) and follow-up after 12 months (T2).

**Discussion:**

Depression is now recognized as a disorder with a high prevalence in primary care but with insufficient treatment response. Case management seems to be a promising intervention which has the potential to bridge the gap of the usually time-limited and fragmented provision of care. Case management has been proven to be effective in several studies but its application in the private general medical practice setting remains unclear.

## Background

Depression is a significant burden of illness [1,2]. Most depressed patients are diagnosed and treated by general practitioners [3,4]. Depression is the third most common reason for a primary care consultation [5]. Patients with depression account for 50% higher health care costs patients than patients who are not depressed [6]. When improving primary health care for chronic conditions, a number of problems have to be resolved: discontinuity and fragmentation of the process of care, lack of co-ordination between different providers, and "the tyranny of urgency" [7]. In the management of depression, these deficits lead to frequent interruption or premature termination of drug therapy, which increases the risk of unfavourable depression outcomes [8,9]. Patient-centred approaches with a focus on empowerment and self management have been recommended [10,7,11]. Case Management may be one approach to improve depression care. Case Management has been defined as "taking responsibility for following-up patients; determining whether patients were continuing the prescribed treatment as intended; assessing whether depressive symptoms were improving; and taking action when patients were not adhering to guideline based treatment or when they were not showing expected improvement" [12]. Case Management consists of five essential components: (1) identification of patients in need of services, (2) assessment of individual patient needs, (3) developing a treatment plan, (4) coordination of care, and (5) monitoring outcomes and altering care when favourable outcomes are not achieved [13].

Reviews of controlled trials including our meta-analysis concluded that Case Management improves patient outcomes – with a moderate effect [12,14,15]. However, most of the studies available were conducted in highly organized Health Maintenance Organizations (HMO) setting using central based stuff to run the intervention. However, it still remains unclear what the effects in a peripheral setting as a private general practice based case management for patients with depression will be like.

## Methods/Design

### Aim of the study

The study examines the efficacy of a GP based case management intervention for patients with depression.

### Scientific hypothesis

Case management (intervention) leads to greater reductions in depressive symptoms than usual care (control group). We hypothesize further that case management leads to a greater increase in adherence (medication) and quality of life.

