### Sample size

Sample size calculations for cluster randomized trials differ completely from sample size calculations for common RCTs [16,17]. Based on the main outcome parameter depression symptom and the main outcome-assessment instrument (GERMAN-PHQ) [18] we performed a power calculation with the method of Hayes and Bennett [19]. It is provided to record a clinical relevant intervention effect of the Case Management from yet 10% up to the primary size, thus an improvement of the depression score (PHQ-D). Assuming an effect of 35 % (PHQ – Score difference from 18,6 to 12.9) in intervention group and a effect of 25 % in control [20] (PHQ Score – 18.6 to 12.9) we have to detect a minimal difference of 1,86. With an alpha of 5%, a beta of 20%, a SD of 6.1 and a ICC 0.1 we are calculating N = 680 (drop-out 30% included). Every arm of the study (34 practices) has to include 10 Patients.

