### Recruitment of GPs and randomization

As described above, the GPs form the unit of randomization (cluster). It was decided to address and to include only those practices that have a contract with all German insurances, because 90 % of care provision is covered by this type of practices. About 1600 GPs in the city of Frankfurt and the region near by (federal state of Hessen) were informed by mail about the study and invited to a meeting. After this meeting, 72 GPs gave their written consent to participate in the study. Based on detailed information about the practice and the GP, the inclusion criteria were checked (no exclusive clinical specialization) and two practices had to be excluded due to the inclusion criteria. The 70 GPs were stratified according to the size of the city where the practice is located and then randomized to the intervention group or the control group. The procedure was done by an independent assistant who is not familiar to one of the participating doctors and is not a person of the project team. A randomization protocol was written. (Figure 1)

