### Outcome-parameter

Table 1 displays the outcome parameters and additionally used instruments. The primary outcome is the depression score assessed by the PHQ-9 questionnaire. The PHQ is an internationally applied instrument for the screening in primary care of the major mental disorders. The German version is also validated [18]. Secondary outcomes include:

**Table 1 T1:** Outcomes and instruments

**Outcome-Parameter (Patient)**	**Instrument**

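### The 80% power at N = 680 holds only with no drop-out; at the stated 30% loss it is about 75%, and the T0 PHQ-9 that could recover it is not used

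*Protocol article*

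**What the plan says.** The Scientific hypothesis section expects "greater reductions in depressive symptoms" from case management than from usual care. The Outcome-parameter section says: "The primary outcome is the depression score assessed by the PHQ-9 questionnaire". Assessments are at T0, 6 months and 12 months.

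The Sample size section builds the target from percentage improvements on a starting score of 18.6: "Assuming an effect of 35 % (PHQ – Score difference from 18,6 to 12.9) in intervention group and a effect of 25 % in control", and concludes that "we have to detect a minimal difference of 1,86". The other inputs are: "With an alpha of 5%, a beta of 20%, a SD of 6.1 and a ICC 0.1", used with the method of Hayes and Bennett. The result is 680 patients, said to include 30% drop-out, from 34 practices per arm with 10 patients each. The section does not say whether the 5% is one- or two-sided, or which quantity has an SD of 6.1.

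Under Recruitment of GPs and randomization, the practices were "stratified according to the size of the city where the practice is located". The article gives no analysis model for the PHQ-9, so it neither plans nor rules out adjustment for T0 or for the stratum.

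**The concern.** The power statement claims to allow for losing three patients in ten. If the arithmetic contains no such allowance, the trial falls short of its own target as soon as the expected loss occurs.

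The claim is also hard to tie to an analysis. The required SD differs between a raw follow-up score, a change from T0 and a baseline-adjusted score, and the section gives one SD without a label. The T0 PHQ-9 is part of the baseline assessment and is the obvious way to recover precision without recruiting more patients, yet the calculation does not mention it.

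A second reason to use T0 comes from the design. Practices recruit the patients, and the Timeframe section implies that randomisation came first. Randomising practices does not by itself make the recruited patients comparable in severity, so some imbalance in T0 PHQ-9 between the arms is possible.

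**Working it through.** **Inputs.** From Sample size: difference d = 1.86, SD = 6.1, ICC = 0.1, alpha 5%, power 80%, 34 practices per arm, 10 patients per practice, 30% drop-out. Assumed: a two-sided test; 7 evaluable patients per practice after 30% loss; a T0-to-follow-up correlation r, which the protocol does not give.

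**The target difference.** 35% off 18.6 leaves 18.6 x 0.65 = 12.09, and 25% off leaves 18.6 x 0.75 = 13.95. The difference is 13.95 - 12.09 = 1.86, as stated. The printed endpoint of 12.9 for both arms is a reduction of 5.7/18.6 = 31% and matches neither percentage.

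**Reproducing 680.** Without clustering, n per arm = 2 x 6.1² x (1.96 + 0.84)² / 1.86² = 168.8. Multiply by the design effect 1 + (m - 1) x 0.1, divide by m, and add one practice per arm (Hayes and Bennett):

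- m = 10: 168.8 x 1.9 / 10 + 1 = 33.08, rounded up to 34 practices. 34 x 10 x 2 = 680, with no drop-out.
- m = 7: 168.8 x 1.6 / 7 + 1 = 39.59, rounded up to 40 practices. 40 x 10 x 2 = 800 recruited.

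**Power at 34 practices per arm.** SE = SD x sqrt(2 x (1 + (m - 1) x 0.1) / (34m)); power = Phi(1.86/SE - 1.96).

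- m = 10: SE = 0.645, power 82.2%.
- m = 7: SE = 0.707, power 74.8%.

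A t-based calculation with 66 degrees of freedom gives 81.1% and 73.6%.

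**Adjusting for T0 at 34 x 7.** If 6.1 is the SD of a raw follow-up score and the ICC stays at 0.1, the adjusted SD is 6.1 x sqrt(1 - r²). If T0 explains only within-practice variance, the between-practice part (0.1 x 6.1² = 3.72) stays, the within-practice part is 0.9 x 6.1² x (1 - r²), and SE = sqrt(2 x (between + within/7) / 34).

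| r (assumed) | Adjusted SD | Power, ICC held at 0.1 | Power, within-practice gain only |
|---|---|---|---|
| 0 (unadjusted) | 6.10 | 75% | 75% |
| 0.2 | 5.98 | 77% | 76% |
| 0.3 | 5.82 | 79% | 77% |
| 0.4 | 5.59 | 82% | 79% |
| 0.5 | 5.28 | 86% | 81% |

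**Correlation needed for 80%.** With the ICC held at 0.1, SE must fall to 1.86/2.80 = 0.664, so sqrt(1 - r²) = 0.664/0.707 and r = 0.34. Keeping the Hayes and Bennett extra practice requires 38.59 x (1 - r²) = 33, so r = 0.38. About 0.4 is a fair working figure. With a within-practice gain only, between + within/7 must fall to 17 x 0.664² = 7.49, which needs r = 0.46.

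The gain from the city-size stratum cannot be computed, because no figure is given for it.

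**The case against.** **This belongs to the SAP.** Covariates and the form of the model are commonly left out of an article, and their absence here is not an error. That stands. The error is the power statement; the adjustment is a recommendation attached to it.

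**A reader might infer that the hypothesis contradicts the sizing,** one being about reductions and the other about an unadjusted score. The protocol does not support this. With a common starting value, 1.86 is both the difference in reductions and the difference in follow-up scores. Nor does the protocol say that 6.1 is a raw-score SD.

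**A reader might also infer that analysing reductions costs power.** That needs three things the protocol does not state: that 6.1 is a raw SD (equal at T0 and follow-up), that an unadjusted change score is analysed, and that r is below 0.5. At r = 0.5 the change score has the same 75% at 34 x 7 as the raw score; at r = 0.7 it has 92%.

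**The test might be one-sided.** Sidedness is not stated and the hypothesis is directional. One-sided at 5%, power at 34 x 7 is 83.8%, and n per arm before clustering is 133.0. Then 133.0 x 1.9 x 1.3 / 10 + 1 = 33.85 also rounds to 34. This stands as a reservation: it needs an unstated one-sided test and a 1.3 inflation, whereas a 30% loss calls for division by 0.7. The two-sided reading gives 680 from the stated inputs with no further step except that drop-out is left out.

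**70 practices were randomised, not 68.** With 35 per arm and 7 evaluable patients each, two-sided power is 76.1%, so this does not close the gap.

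**Adjustment should not be oversold as removing bias.** It corrects imbalance in measured T0 severity only. Other differential selection by practices remains, and the protocol does not say when practices learned their allocation.

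**Conclusion.** The statement of 80% power at 680 with 30% drop-out included is not supported by its own inputs, taken two-sided. They give 680 only with complete follow-up. At 34 x 7 per arm power is about 75% (74% with the t distribution), and 80% would take 800 recruited patients.

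The undefined SD is a real gap, because the meaning of the power figure depends on it. Using T0 PHQ-9 is a sensible remedy, not a guaranteed one. It restores 80% at 34 x 7 if r is about 0.4 or more with the ICC held at 0.1, and needs about 0.46 if T0 explains only within-practice variance. At r = 0.2 it adds only about 2 points. These adjusted figures also assume that 6.1 is a raw-score SD. If 6.1 is already a residual SD, the gain has been counted and power stays at about 75%.

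**What to change.** 1. Restate the power at 34 practices x 7 evaluable patients per arm, and say whether the 5% is one- or two-sided.
2. Say whether the SD of 6.1 belongs to a follow-up score, a change from T0 or a residual after adjustment. Correct the printed endpoints so that they agree with 35% and 25%.
3. State the primary comparison as follow-up PHQ-9 between arms, with a practice effect, adjusted for T0 PHQ-9 and the city-size stratum. Give the assumed correlation and show power over a range such as 0.2 to 0.5.

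The cost is wording and a recalculation, with no new data, patients or visits. It is not quite free: the stratum uses a few degrees of freedom, missing T0 scores need a stated rule, and the restated power will be below 80% if the correlation is below about 0.4. About 220 patients had completed baseline when the article was written, so enrolment was still under way. If the full protocol or SAP already specifies the adjustment, only items 1 and 2 are needed.

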### Study design

The study is a (prospective) cluster-randomized two-armed intervention study with the practices being clusters. The design of a cluster randomized study was chosen because with this type of study internal validity (absence of confounders) can be optimized, contamination of interventions associated with patient randomization is not possible.

### Sample size

Sample size calculations for cluster randomized trials differ completely from sample size calculations for common RCTs [16,17]. Based on the main outcome parameter depression symptom and the main outcome-assessment instrument (GERMAN-PHQ) [18] we performed a power calculation with the method of Hayes and Bennett [19]. It is provided to record a clinical relevant intervention effect of the Case Management from yet 10% up to the primary size, thus an improvement of the depression score (PHQ-D). Assuming an effect of 35 % (PHQ – Score difference from 18,6 to 12.9) in intervention group and a effect of 25 % in control [20] (PHQ Score – 18.6 to 12.9) we have to detect a minimal difference of 1,86. With an alpha of 5%, a beta of 20%, a SD of 6.1 and a ICC 0.1 we are calculating N = 680 (drop-out 30% included). Every arm of the study (34 practices) has to include 10 Patients.

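### The 680 patients said to allow for 30% drop-out are, on a two-sided 5% test, what the stated inputs require with no drop-out; with that loss, power is about 74–76%, not 80%

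*Protocol article*

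**What the plan says.** The sample size section of the protocol article names its approach: "we performed a power calculation with the method of Hayes and Bennett". The target is explicit: "we have to detect a minimal difference of 1,86", which is 10% of the baseline score of 18.6 (35% improvement against 25%). The error rates are given as "With an alpha of 5%, a beta of 20" per cent, without saying whether the test is one- or two-sided. The remaining inputs and the result follow: "a SD of 6.1 and a ICC 0.1 we are calculating N = 680 (drop-out 30% included"). The section then sets the layout: "Every arm of the study (34 practices) has to include 10 Patients". Read with the abstract, where each GP includes 10 patients, this means 10 recruited per practice, and 34 × 10 × 2 = 680.

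The section on recruitment and randomisation reports slightly more practices than planned: "The 70 GPs were stratified according to the size of the city where the practice is located". The number allocated to each arm is not given.

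**The concern.** Every input to the calculation is printed, so the result can be checked. Ten is the number recruited per practice, so a 30% loss has to come out of those ten. If the formula returns 680 only when all ten are analysed, the text claims an allowance that the number does not contain.

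What is at stake is how a null result would be read. A reader would take the chance of missing a true 1.86-point difference to be at most 20%, even after the expected losses. On a two-sided test it would be about 24% to 26%. The validity of the treatment estimate and the type I error are not affected.

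**Working it through.** **Inputs (all from the sample size section unless noted).** Difference 1.86; SD 6.1, taken as the total SD; ICC 0.1; alpha 5%; power 80%; 10 recruited per practice; 34 practices per arm; drop-out 30%. *Assumptions:* two-sided test; drop-out spread evenly within practices, leaving m = 7 analysed; the 70 randomised practices split 35 and 35.

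**Variance components.** Total 6.1² = 37.21; between practices 0.1 × 37.21 = 3.721; within practices 33.489.

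**Practices per arm, c (Hayes and Bennett, means):** c = 1 + (1.960 + 0.842)² × 2 × (3.721 + 33.489/m) / 1.86², with (1.960 + 0.842)² = 7.849. Equivalently, take 168.84 patients per arm for an individually randomised trial, multiply by the design effect 1 + (m − 1) × 0.1, divide by m and add 1.

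*Reproducing the plan's figure, m = 10:* 168.84 × 1.9 = 320.8; /10 = 32.08; + 1 = 33.08, so 34 per arm and 34 × 10 × 2 = **680**. Both printed figures are matched.

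*With 30% drop-out, m = 7:* 168.84 × 1.6 = 270.1; /7 = 38.59; + 1 = 39.59, so 40 per arm and 40 × 10 × 2 = **800** recruited. The planned 34 × 7 = 238 analysed per arm falls short of 270 even before the extra practice is added.

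**Power.** The variance of a practice mean is V = 3.721 + 33.489/m, which is 7.070 for m = 10 and 8.505 for m = 7. Power = Φ(1.86 / √(2V/k) − 1.960), with k = c − 1 for Hayes and Bennett and k = c for the plain normal approximation. A cluster-level t calculation agrees with the first to the decimal shown.

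Worked case, 34 × 7: √(2 × 8.505/33) = 0.718; 1.86/0.718 = 2.591; 2.591 − 1.960 = 0.631; Φ = 0.736.

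| Practices per arm × analysed | Hayes–Bennett or t | Plain normal |
|---|---|---|
| 34 × 10 | 81.1% | 82.2% |
| 34 × 7 | 73.6% | 74.8% |
| 35 × 10 | 82.2% | 83.3% |
| 35 × 7 | 74.9% | 76.1% |
| 40 × 7 | 80.4% | 81.4% |

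With 7 analysed per practice, the difference detectable with 80% power is about 2.0 points. For 680 truly to include 30% drop-out at 34 practices per arm, the ICC would have to be about 0.06 to 0.07 rather than 0.1. If the loss came as whole practices instead (about 24 per arm with 10 each), power would be about 66% to 68%.

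**Sensitivity to sidedness (one-sided 5%).** With m = 7, c = 31.40, so 32 per arm and 640 patients, not 680. Power would be about 83–84% at 34 × 7 and about 84–85% at 35 × 7.

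**The case against.** The strongest reply is that the article never says two-sided, and its hypothesis is directional: "Case management (intervention) leads to greater reductions in depressive symptoms than usual care (control group"). A one-sided route also reaches the printed number. With m = 10 the requirement is 25.27 practices; × 1.3 for drop-out gives 32.85; + 1 gives 33.85, so 34 per arm and 680. This weakens any claim to know how 680 was obtained. A reader might infer from the exact match that drop-out was certainly left out, or that the design lacks 80% power whatever test is used. The article supports neither without the two-sided assumption.

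The reply does not rescue the sentence, however. A directional hypothesis is not a declared one-sided test. The one-sided route also needs a second step that is wrong, since allowing for 30% loss means dividing by 0.7, not multiplying by 1.3. Done correctly, one-sided testing gives 640 with 7 analysed per practice, or 25.27/0.7 + 1 = 37.10, so 38 practices and 760 patients, if the 10-patient figure is inflated. Neither is 680.

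Three further objections stand. Since 70 practices are already randomised, 75–76% describes this trial better than 74%. The shortfall arises in full only if the whole 30% is lost. And the article states no primary analysis model, so the absence of a baseline covariate is not an error in it.

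**Conclusion.** As written, the statement that 680 includes 30% drop-out does not follow from the stated inputs and method. On a conventional two-sided 5% test, 680 is the requirement with complete follow-up, and 800 is the requirement with 7 of 10 patients analysed per practice. With the expected loss, power is about 74–75% at 34 practices per arm and about 75–76% at 35 per arm, a shortfall of roughly 4 to 6 percentage points from 80%.

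This rests on two-sided testing, 6.1 being the total SD, even loss within practices and, for the second figure, an equal split of the 70 practices. Under a one-sided 5% test, power would be about 83–85%, so sidedness must be stated before any power figure can be relied on. The section prints the same score change for both arms, but this does not affect the check, because 1.86 is given outright and equals 10% of 18.6.

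A reader might also infer that adjusting for baseline PHQ-9 would restore 80%. The article does not support that promise: it gives no correlation between baseline and follow-up and does not say what 6.1 is the SD of.

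**What to change.** In the sample size section:

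- delete the claim that 30% drop-out is included in 680;
- state that the 5% test is two-sided;
- restate power as about 81–82% with complete follow-up at 34 practices per arm (82–83% at 35), and about 74–76% with 30% drop-out across 34 to 35 practices per arm.

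This is a rewording. It needs no extra patients or practices and can be done now, as only about 220 patients had been included when the article was written. The cost is a slightly less favourable stated power.

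*Optional:* adjust the primary cluster-level analysis for the T0 PHQ-9, which is already collected, without promising 80%. The gain depends on an assumed T0-to-follow-up correlation r and on which variance component falls. The figures below are for 34 × 7 per arm, two-sided, cluster-level t. They hold only if 6.1 is an unadjusted follow-up SD.

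| Assumed r | Only within-practice variance falls: V = 3.721 + (1 − r²) × 33.489/7 | Both components fall equally: V = (1 − r²) × 8.505 |
|---|---|---|
| 0.3 | about 76% | about 78% |
| 0.4 | about 78% | about 81% |
| 0.5 | about 80% | about 85% |
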